#### Parents

A parent-teacher conference will take place at the class level to emphasize the importance of physical activity throughout the entire life and give parents ideas of how to support their children in establishing a physically active lifestyle. In addition, parents will receive information material about the program and the assessments. To take parents with a foreign background into account, materials will also be available in Turkish and Russian as the most frequently spoken foreign languages in Germany.

### Study design

The effectiveness of the “läuft.” physical activity program will be tested in a two-arm three-wave cluster randomized controlled trial. Data of the different waves are hypothesized to be clustered at the individual, class and school level. Schools are the units of randomization and will be randomly allocated to the intervention and control group. In intervention schools the “läuft.” physical activity program will be implemented, while schools of the control group run through the usual curriculum and will receive no further intervention. In both groups, fitness, medical and questionnaire data will be collected for three times: “baseline” (immediately before the intervention), “post” (immediately after the intervention) and “follow-up” (12 months after the end of the intervention) assessment. In addition, after the intervention, qualitative analyses will be conducted in classes of the intervention group to gain insight into interactive processes within the classes and to reconstruct subjective experiences and interpretations of activating-strategies.

Process evaluation of the planned trial will be realized through questionnaires and interviews during and after the study, respectively. The study design is presented in Figure 2.

**Figure 2 F2:**
[figure not shown]
Study design.

### Sample size calculation

There are specific constraints for analysis of cluster randomized trials [26] since the responses of individuals within a cluster tend to be more similar than those of individuals of different clusters. This clustering effect can be defined as 1 + (m-1)p, where m is the average number of subjects per cluster and p the intraclass correlation coefficient (ICC) [27]. The ICC for physical fitness and adiposity was taken from another cluster randomized controlled trial, the Kindersportstudie (KISS) [28,29] and estimated with approximately 0.05 (p). Assuming an equal average cluster size of 20 pupils with parental consent (m = 20), a clustering effect of 1.95 was determined. Without taking into account the clustering of the data, assuming a small to medium effect size of the intervention (Cohen’s d = 0.30) on physical activity as one primary and the most important outcome being still detectable at follow-up, applying a significance level of alpha = 0.05 and power = 0.80, it can be estimated that N = 350 pupils are required to detect a difference between two independent sample means [30,31]. Taking the cluster effect into account, a required sample size of N = 683 students and 34 classes was determined. A computerized sample size calculator for cluster randomized trials was used to confirm this estimation [32].

Based on earlier experiences [33,34], a drop-out rate of 25% over the study was hypothesized. Hence, a total sample size of 911 pupils and 46 classes will be recruited for baseline to detect possible differences between the groups at follow-up. In order to recruit the estimated sample size of 46 classes while assuming a participation rate of 20% and an average of at least two participating classes per school, about 100 schools will be invited to participate.

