### Statistical analysis

Statistical analysis will be conducted with Stata V13.1 (Stata Corp, College Station, TX, USA) following the intention to treat principle. To evaluate efficacy of the program, multilevel analysis with the levels: schools, classes, individuals and waves, will be performed. Random intercepts will be included for schools, classes and individuals taking the clustering effect into account. Group and covariates will be taken as fixed effects. Differences between intervention and control group at baseline as well as attrition analysis will be examined using a t-test for independent samples and Fisher’s exact test.

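### The sample size takes the class as the cluster although schools are randomised, so the stated 80% power for d = 0.30 is not supported

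*Protocol article*

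**What the plan says.** All references are to the protocol article.

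- **Sample size calculation** gives the inflation factor: "This clustering effect can be defined as 1 + (m-1)p, where m is the average number of subjects per cluster". It then sets the cluster size: "Assuming an equal average cluster size of 20 pupils with parental consent". With an ICC of about 0.05 this yields 1.95. The unclustered requirement is stated as "it can be estimated that N = 350 pupils are required to detect a difference between two independent sample means", at d = 0.30 and "applying a significance level of alpha = 0.05 and power = 0.80". The clustered requirement is 683 pupils in 34 classes. Allowing for 25% drop-out, it becomes 911 pupils in 46 classes. The same section assumes "an average of at least two participating classes per school".
- **Study design** states: "Schools are the units of randomization and will be randomly allocated to the intervention and control group". It also expects the data to be correlated at individual, class and school level.
- **Randomization** repeats that allocation is by school and sets a 3:2 ratio in favour of the intervention.
- **Statistical analysis**: "Random intercepts will be included for schools, classes and individuals".

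**The concern.** The variance of the treatment comparison depends on how alike pupils are within the unit that is randomised. Here that unit is the school, with two or more classes of about 20 pupils, so roughly 40 pupils or more. The 46 classes amount to about 23 schools. A design effect built on m = 20 treats two classes of the same school as independent. The article does not believe that itself: it expects school-level clustering and fits a school intercept. The analysis will therefore carry a variance component that the sample size sets to zero.

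At stake are the required number (683), the recruitment target (911) and the claim of 80% power at the 12-month follow-up for physical activity, which the article calls its most important outcome. If the true power is lower, a non-significant result says less against an effect of d = 0.30 than the stated 80% suggests.

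**Working it through.** **1. Reproduce the plan's figures.** Inputs from the sample size section: d = 0.30, alpha 0.05 (taken as two-sided, which reproduces the plan), power 0.80, ICC 0.05, m = 20, drop-out 25%.

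- Per arm: 2 x (1.96 + 0.8416)^2 / 0.30^2 = 174.4, so 175, or 350 in total.
- Design effect: 1 + 19 x 0.05 = 1.95.
- 350 x 1.95 = 682.5, so 683; 683/20 = 34 classes.
- 683/0.75 = 911; 911/20 = 46 classes.

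Everything reproduces, with the class as cluster and equal arms. The arithmetic is right; the cluster unit is the problem.

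**2. Formulas for the check.** Take m pupils per class and k = 2 classes per school. Let rho_class be the correlation within a class and rho_school the correlation between pupils in different classes of the same school:

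DE = 1 + (m-1) x rho_class + m(k-1) x rho_school

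At 3:2, the standardised effect over its standard error is 0.30 x sqrt(0.24 x 683/DE), where 0.24 = 0.6 x 0.4. Normal power uses the critical value 1.96. The t version uses the noncentral t with schools minus 2 degrees of freedom.

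Two drop-out patterns bracket the 683 analysed pupils:

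- *Whole schools lost*: classes stay at 20, 683/40 = about 17 schools, 15 df.
- *Loss spread evenly*: 23 schools remain with 683/23 = 29.7 pupils each, or 683/46 = 14.8 per class, 21 df.

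**3. If 0.05 applies across the whole school** (rho_class = rho_school = 0.05):

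- Whole schools lost: DE = 1 + 39 x 0.05 = 2.95. Effective N = 683/2.95 = about 232, against 350 needed. The ratio is 0.30 x sqrt(0.24 x 231.5) = 2.24, so power is 0.61 (normal) or 0.55 (t).
- Loss spread: DE = 1 + 28.7 x 0.05 = 2.43. Effective N is about 281, the ratio is 2.46, and power is 0.69 (normal) or 0.65 (t).
- With equal arms the normal figures are 0.63 and 0.71.
- Keeping 80% at m = 40 and equal arms would take 350 x 2.95 = 1,033 analysed pupils.

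**4. If 0.05 is the within-class value** and rho_school is lower (assumed 0.01 to 0.03; the article gives no figure), at 3:2:

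| rho_school | DE, classes of 20 | Power normal / t (15 df) | DE, classes of 14.8 | Power normal / t (21 df) |
|---|---|---|---|---|
| 0 | 1.95 | 0.79 / 0.73 | 1.69 | 0.84 / 0.80 |
| 0.01 | 2.15 | 0.75 / 0.69 | 1.84 | 0.81 / 0.77 |
| 0.02 | 2.35 | 0.71 / 0.65 | 1.99 | 0.78 / 0.74 |
| 0.03 | 2.55 | 0.67 / 0.61 | 2.14 | 0.75 / 0.71 |

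**5. Detectable effect at 80% power, 3:2.** By normal approximation this is 2.80 x sqrt(DE/(0.24 x 683)). At DE = 1.84 it is 0.30, at 2.43 it is 0.34 and at 2.95 it is 0.38. With 15 df the last figure becomes 0.40.

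**The case against.** Several points on the other side carry weight.

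- **The level of the ICC is not stated.** Using 0.05 with m = 20 pupils per class suggests a within-class value. Applying the same 0.05 between classes assumes that classmates are no more alike than schoolmates, whereas the article expects class and school components. The figures in step 3 are therefore a severe case and not the base case. This stands.
- **The plan has some slack.** It keeps m = 20 after allowing for 25% drop-out. If the loss thins every class, the class-level design effect is smaller than 1.95, which offsets part of the omission. This stands, and it is why the upper end of step 4 touches 80%.
- **The 0.55 combines two things that may not coincide.** The 3:2 ratio is chosen because more intervention schools are expected to leave. If whole schools leave in that way, the analysed ratio moves towards 1:1, where the figure is 0.57. The difference is minor.
- **Baseline adjustment and repeated waves may recover precision.** If adjustment cut the variance by 25% at all levels (a correlation of 0.5, an assumption), the two t figures in step 3 would rise to about 0.68 and 0.77. The article's calculation compares two independent means and claims no such gain, so this softens the size without supporting the 80%.
- **A sample size calculator confirmed the result, and the model is multilevel.** Neither helps. A calculator given m = 20 repeats the same input, and the school intercept addresses the validity of the test, not its power.

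A reader might infer that the trial certainly has only 55-70% power. The documents do not support that, because it needs the 0.05 to hold between classes as strongly as within them. Nor do they support reading the planned analysis as invalid, since it includes the randomised unit.

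**Conclusion.** The point holds as a mismatch between the sample size calculation and the design. The calculation uses the class, the trial randomises schools, and no between-class term enters the design effect. The stated 80% power for d = 0.30 with 683 analysed pupils is therefore unsupported. The mismatch is clear, but its size is not fixed by the article. Over the cases considered, power at 3:2 runs from about 0.55 (0.05 across the whole school, whole schools lost, t on 15 df) to about 0.81 (0.05 within class, 0.01 between classes, loss spread evenly, normal approximation). At 3:2, power reaches 80% only when the between-class correlation is near zero and the loss is spread over all classes; on the t reference this needs a correlation of zero. That sits badly with the school-level clustering the article expects. All figures assume two classes per school and no gain from covariates.

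**What to change.** Recompute with the school as the randomised cluster, using 1 + (m-1) x rho_class + m(k-1) x rho_school as defined above. In the text:

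- say whether the ICC of 0.05 is a class or a school value, and state the assumed correlation between pupils in different classes of the same school;
- use the 3:2 ratio and schools-minus-2 degrees of freedom;
- give the number of schools, about 23 at baseline, alongside the number of classes;
- replace the single 80% with the resulting power range, or with the detectable effect (about 0.30-0.40 depending on these assumptions), and say that it is before any gain from baseline adjustment.

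The cost is a rewritten paragraph and probably a less favourable stated power. No extra schools are needed to correct the figure. The article reports that school recruitment had not begun at submission, so the sponsor could also choose to revisit the target, but that is a separate decision.

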### Procedure and participants

The study has been approved by the ethics committee of the German Psychological Society as well as the Ministry of Education and Science of Schleswig-Holstein. It targets 8^th^ grade classes with students aged 12 up to 15 years in secondary schools in the federal state of Schleswig-Holstein in Germany. Schools will be selected from a complete list of all secondary schools in Schleswig-Holstein obtained from the Ministry of Education. All types of schools will be included, except schools for disabled students. In order to recruit a study sample of 46 classes, about 100 schools will be invited to participate. An invitation letter and information sheets about the aims, methods and requirements of the study will be sent to the head of each school. Copies of the letters of approval by the Ministry of Education and the ethics committee will be attached. Schools agreeing to participate must send back their written consent indicating the acceptance of study characteristics (including randomization), number of grade 8 classes eligible for the study, names of the class teachers, and number of students per class. All students of participating classes will be included in the study. Schools not agreeing to participate are requested to explain their denial. In order to conduct non-responder analysis, all invited schools will be asked to provide some basic data about type and size of school, number of grade 8 classes, gym and sports equipment, sports facilities on the school ground and offered sports events, projects and courses. Participating schools will be stratified (type of school and number of grade 8 classes) and randomly allocated to the intervention and the control groups. Furthermore, parents will receive information sheets about the study and will be asked for informed consent to the storage and use of assessed data of their children. Teachers will register all names of students with no permission in a list which they keep throughout the entire trial. Students with refusals will take part in the assessment but their data will not be registered.

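### At the plan's stated minimum of two classes per school, about 100 invitations give about 40 classes, 6 short of the 46 they are meant to deliver

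*Protocol article*

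**What the plan says.** The Sample size calculation section of the protocol article ends its derivation with a commitment that "a total sample size of 911 pupils and 46 classes will be recruited for baseline". It then turns classes into invitations, with the inputs and the result printed in the same sentence: "assuming a participation rate of 20% and an average of at least two participating classes per school, about 100 schools will be invited". The Procedure and participants section repeats the pairing without the inputs: "In order to recruit a study sample of 46 classes, about 100 schools will be invited to participate".

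Two is the only value given anywhere for participating classes per school. It is worded as a lower bound on the average, and the number of invitations is worded as approximate.

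**The concern.** A number of invitations justified by a minimum ought to reach the target at that minimum. Here it does not, and no expected average above two is given that would close the gap. The mismatch sits between figures printed side by side, so it cannot be put down to detail left for a fuller protocol or an analysis plan.

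At stake is whether the recruitment effort is large enough to deliver the sample on which the stated power rests. Schools are the units of randomization, and the Randomization section already expects more schools to drop out of the intervention group, so there is little reason to begin without margin.

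**Working it through.** **Inputs, all from the Sample size calculation section unless noted.** Effect size d = 0.30; alpha 0.05 (taken as two-sided, which is not stated but reproduces the plan's figure); power 0.80; ICC 0.05; 20 pupils per class; dropout 25%; participation 20%; at least two classes per school; about 100 schools invited. Allocation 3:2, from the Randomization section.

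**1. Reproducing the plan's own chain.**
- Unclustered size per arm: 2 × (1.960 + 0.842)² / 0.30² = 174.4, so 175 per arm and 350 in total. This agrees with "N = 350 pupils are required to detect a difference between two independent sample means".
- Design effect: 1 + (20 − 1) × 0.05 = 1.95.
- Clustered size: 350 × 1.95 = 682.5, so 683 pupils; 683 / 20 = 34.15, given as 34 classes.
- Allowing for dropout: 683 / 0.75 = 910.7, so 911 pupils; 911 / 20 = 45.55, so 46 classes.

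The totals of 350, 683 and 911 pupils and the 46-class target all reproduce.

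**2. The recruitment step.**
- Classes obtained = invitations × participation × classes per school = 100 × 0.20 × 2 = 40.
- Shortfall: 46 − 40 = 6 classes; 6 / 46 = 13%.
- Invitations needed at two classes per school: 46 / (0.20 × 2) = 115.
- Classes per school needed with 100 invitations: 46 / (100 × 0.20) = 2.3.
- Participation needed with 100 invitations and two classes per school: 46 / (100 × 2) = 23%.

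Sensitivity with 100 invitations and 20% participation:

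| Average classes per school | Classes obtained |
|---|---|
| 2.0 | 40 |
| 2.3 | 46 |
| 2.5 | 50 |
| 3.0 | 60 |

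**3. What a 40-class baseline would mean.**
- Pupils at baseline: 40 × 20 = 800, against 911.
- After 25% loss: 800 × 0.75 = 600, against 683.

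Power is taken from the normal approximation. At equal allocation it is Φ(0.30 × √N / 2 − 1.960), where N is the effective number of pupils. At 3:2, √N × √(0.6 × 0.4) replaces √N / 2.

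| Classes | Completers | Design effect | Effective N | Power 1:1 | Power 3:2 |
|---|---|---|---|---|---|
| 46 | 46 × 20 × 0.75 = 690 | 1.95 | 354 | 0.81 | 0.79 |
| 40 | 600 | 1.95 | 308 | 0.75 | 0.73 |
| 46 | 690 | 1.70 | 406 | 0.86 | 0.84 |
| 40 | 600 | 1.70 | 353 | 0.80 | 0.79 |

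The design effect of 1.95 holds if classes that remain keep 20 pupils, that is, if losses remove whole classes. If the 25% loss is spread evenly, each class keeps 15 pupils and the plan's formula gives 1 + (15 − 1) × 0.05 = 1.70.

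**The case against.** The strongest reply is that the inputs are not point values. Two is a floor on the average and 100 is a round figure, so the plan implies at least about 40 classes rather than exactly 40. An average of 2.3 satisfies the wording and gives exactly 46. The commitment is to 46 classes, and the invitations are only the means. Nothing says that recruitment stops after 100 letters, schools come from a complete state list, and recruitment runs for several months. **This stands.** A reader might infer that the trial will start with 40 classes, or that its sample size is wrong. The documents support neither reading.

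A reader might also take the power to be 0.75, or 0.73 under the planned allocation, instead of 0.80. That too goes further than the documents allow:
- It requires an average of exactly two classes and no further invitations.
- It requires losses to fall as whole classes. With losses spread within classes, 40 classes still give about 0.80 at equal allocation.
- The 3:2 allocation lowers power by itself. With 350 effective pupils it gives about 0.785, so the drop from 0.80 to 0.73 combines two separate effects.

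Nor does the plan set a target number of schools. The figure of 23 schools (46 / 2) exists only if the average is exactly two, so it should not serve as a recruitment threshold.

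**What the reply does not remove** is that the one value offered in support of about 100 invitations does not support it. The word for approximate is weak cover: 115 is 15% more than 100, in a paragraph that otherwise rounds 682.5 to 683 and 45.55 to 46.

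**Conclusion.** Wrong as written, and minor. At the stated minimum of two classes per school and 20% participation, about 100 invitations deliver about 20 schools and 40 classes, 13% below the 46 they are meant to produce. The gap closes with about 115 invitations, or with an average of 2.3 classes per school, which the text allows but nowhere assumes.

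The consequence is conditional. If 40 classes were all that joined, power at equal allocation would lie between about 0.75 (whole classes lost) and about 0.80 (losses spread within classes). With the dropout pattern and allocation held fixed, having 40 rather than 46 classes costs about 0.05 to 0.06 in power. The upper end is therefore no loss against the nominal 0.80, though it is still below what 46 classes would give. These figures rest on the plan's own d, ICC, class size and dropout, and on a two-sided test.

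**What to change.** Make one of two changes, in both the Sample size calculation and the Procedure and participants sections:

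1. Replace about 100 schools with about 115 schools; or
2. Keep about 100, state that an average of at least 2.3 participating classes per school is assumed, and add that further schools from the state list will be invited if fewer than 46 classes have agreed.

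Any trigger for further invitations should be the number of classes, not a number of schools: under the second option, 20 schools are enough. The further-invitation step is worth adding under the first option too, because 115 meets the target only on average. If schools decided independently at 20%, the chance of at least 23 agreeing would be about 0.54 with 115 invitations, against 0.26 with 100.

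The cost is about fifteen more letters, or one added sentence. The article's Trial status section places its submission before school recruitment began, so the change was feasible at that point. The target, design and analysis are untouched.

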### Procedure and participants

The study has been approved by the ethics committee of the German Psychological Society as well as the Ministry of Education and Science of Schleswig-Holstein. It targets 8^th^ grade classes with students aged 12 up to 15 years in secondary schools in the federal state of Schleswig-Holstein in Germany. Schools will be selected from a complete list of all secondary schools in Schleswig-Holstein obtained from the Ministry of Education. All types of schools will be included, except schools for disabled students. In order to recruit a study sample of 46 classes, about 100 schools will be invited to participate. An invitation letter and information sheets about the aims, methods and requirements of the study will be sent to the head of each school. Copies of the letters of approval by the Ministry of Education and the ethics committee will be attached. Schools agreeing to participate must send back their written consent indicating the acceptance of study characteristics (including randomization), number of grade 8 classes eligible for the study, names of the class teachers, and number of students per class. All students of participating classes will be included in the study. Schools not agreeing to participate are requested to explain their denial. In order to conduct non-responder analysis, all invited schools will be asked to provide some basic data about type and size of school, number of grade 8 classes, gym and sports equipment, sports facilities on the school ground and offered sports events, projects and courses. Participating schools will be stratified (type of school and number of grade 8 classes) and randomly allocated to the intervention and the control groups. Furthermore, parents will receive information sheets about the study and will be asked for informed consent to the storage and use of assessed data of their children. Teachers will register all names of students with no permission in a list which they keep throughout the entire trial. Students with refusals will take part in the assessment but their data will not be registered.

